### Study Design

This study will be implemented as a 2-arm, cluster RCT [28], with an intervention condition (UP-A adapted as a preventive intervention program) and a 3-month WL control condition. Measurements will be taken on the following occasions: (1) Time 1 (1 week before the experimental group starts the intervention); (2) Time 2 (1 week after the experimental group finishes the intervention); (3) Time 3 (3 months after the experimental group finishes the intervention and 1 week before the WL control group starts the intervention); and (4) Time 4 (1 week after the WL control group finishes the intervention). On all occasions, except for Time 4, both groups will complete the outcome measures at about the same time. For Time 4, only the WL control group will complete the outcome measures. This represents a 3 (time) by 2 (group) repeated measures design. The flow diagram of the study is shown in Figure 1.

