Power analyses were conducted using G*Power Version 3 software [67]. Sample size required to detect a Cohen *d* effect of .30 was estimated, based upon effect sizes reported in meta-analyses of school-based anxiety and depression preventive interventions conducted all over the world [68,69], including in Spain [70]. Calculations showed that with a power level of .80 and a significance level of alpha = .05, a total sample of N_Non-cluster_ of 74 was required to detect a significant effect. However, potential loss of power due to data clustering had to be considered in the sample size calculation. The impact of the ICC on the planned trial size depends on the so-called design effect, which can be calculated as 1+(*m*-1) ICC, with *m* referring to the number of participants recruited per cluster [66]. For this study, the ICC is unknown although, on the basis of prior school-based prevention research, the expected ICC for anxiety and depression-related outcomes is approximately 0.02 [27]. The anticipated average class (cluster) size for this study is 27 students meeting inclusion criteria, resulting in a design effect of 1.52. The design effect is then multiplied by the previously calculated N_Non-cluster_ [66], resulting in an estimated sample size for this trial of 112, considering the design effect. In addition, we estimated a dropout rate of 10% based on previous studies [65,71], resulting in an estimated total sample size of 123 (at least 62 students in each group). The total number of clusters required can be calculated dividing the estimated total sample size by the estimated number of participants recruited per cluster (123/27), resulting in 4.56 clusters [66]. Therefore, to achieve a sample of this size, a total of 157 students and 5 clusters were recruited.

As the flow diagram shows (Figure 1), the final number of participants matches these a priori computations closely: 90 students (10 lost at Time 2) were allocated to the preventive intervention group and 62 students (4 lost at Time 2) were assigned to the WL control group. In addition, this study will allow for calculation of the ICC and effect sizes for all primary and secondary outcomes, which could be very important in assisting future researchers in establishing the feasibility and ideal sample size for future full-scale cluster RCTs applying the UP-A as a preventive intervention.

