## Results

Analysis and presentation of data will be in accordance with CONSORT guidelines and, in particular, the extension to cluster randomized trials [28]. Statistical significance will be considered as a *P* value of less than .05, and statistical analysis will be mainly carried out using IBM Statistical Package for the Social Sciences, Version 24.0 (IBM SPSS). Data will be analyzed taking the clustering of students within classes into account.

To check for possible differences at pre-intervention between intervention and WL control groups, a chi-square test for nonparametric variables and a 2-tailed *t* test for continuous variables will be performed at the student-level and class-level on sociodemographic variables as well as on primary and secondary outcome measures. Complete case analyses (excluding participants with missing data), intent-to-treat analyses (including all randomized individuals), and completer status analyses (ie, participants that achieved completer status, that is, participants that attended to 7 or more sessions), will be conducted according to the initial allocation of classes to either preventive intervention or WL control groups. Results will be reported at cluster and individual levels, including information about the estimated effect size and its precision, as well as ICCs for each primary and secondary outcome.

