In relation to missing data, we will follow the guidelines for analyzing and reporting cluster RCTs with missing data established by Fiero and et al [72] and Díaz and et al [73]. Specifically, we will (1) attempt to follow up on all randomized clusters and individuals in order to limit the extent of missing data; (2) report the number of clusters and individuals lost to follow-up, as well as numbers of missing values for each variable of interest, which will be important when deciding what analysis to use; (3) collect and report information about reasons for losses to follow-up and other missing values, which may help when deciding the plausibility of the missing-at-random assumption; (4) justify the choice of principal analysis, the missing data mechanism assumed, and the plausibility of these assumptions; (5) perform and report sensitivity analyses to explore the robustness of the trial results to departures from the missing data assumption made in the primary analysis; and (6) follow the CONSORT extension for cluster trials [28] to ensure comprehensive reporting and transparency of methods used. To investigate the potential effects of missing data, the baseline characteristics of the adolescents will be compared for those with and without missing data.

The effectiveness of the intervention will be assessed using complex samples procedures in SPSS as well as multi-level (or hierarchical) modeling that includes both fixed (intervention effects) and random (students in classrooms) effects. Experimental and WL control groups will be compared at 3 points in time: Time 1 (pre-treatment), Time 2 (post-treatment for intervention group), and Time 3 (3-month follow-up for intervention group). In addition, within-participant analyses will be conducted only with the WL control group at Time 4. ICCs will be calculated for all primary and secondary outcomes to compare the variation due to school class and the total variance.

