Secondary analyses will include (1) repeating the primary analysis adjusting for any variables exhibiting significant imbalance at baseline to assess whether this influences the findings; (2) examining intervention changes for adolescents who scored above the clinical cut-off for anxiety and/or depression at Time 1; (3) investigating potential predictors of intervention effects including all participants (both intervention and WL control groups) after the WL receives UP-A; (4) comparing observed and expected attrition rates, as well as observed and expected ICCs; and (5) analyzing answers to checklists completed by group leaders.

At the time of submitting this manuscript, all participants have been recruited and we have conducted Time 1 and Time 2 assessments with the experimental and WL control groups. The experimental group has also completed the preventive intervention. We expect the WL control group to complete the preventive intervention and Time 4 assessments in July 2017.

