## Discussion

### Principal Findings

This paper describes the study protocol of a cluster RCT testing the first adaptation of the UP-A as a school-based anxiety and depression preventive intervention. The primary outcomes are change in anxiety and depression symptoms. Secondary outcomes include change in participant-identified top problems ratings, conduct problems, hyperactivity/inattention symptoms, peer problems, prosocial behavior, school grades, depression and anxiety-related interference, positive and negative affect, anxiety sensitivity, emotional avoidance, life satisfaction, quality of life, self-esteem, school adjustment, and discipline problems. This study will also improve our understanding of factors that might influence the effectiveness of UP-A through the preliminary examination of a number of potential predictors of treatment outcomes, including age, gender, number of sessions attended, engagement and effort during sessions, understanding of basic program concepts, adherence to home practice, and practice of specific strategies outside of sessions.

This study focuses on a school-based, universal prevention program for anxiety and depression, which has the advantage of being easily integrated into a school curriculum and thereby limiting the extent to which participants are segregated from peers and at risk for possible stigmatization due to their participation [74]. It is surprising that, despite the high co-occurrence between anxiety and depression and their shared risk and vulnerability factors, preventive interventions have typically focused on either depression or on anxiety alone [10]. For instance, of the 30 total studies included in a meta-analysis conducted by Ahlen and colleagues, 13 studies focused primarily on depression prevention, 10 studies focused primarily on anxiety prevention, and only 7 studies focused on prevention of both disorders [27]. A transdiagnostic approach to preventing anxiety and depression may enhance the efficacy, generalizability, and cost-effectiveness of prevention programs [10], as well as prevent the development of related emotional disorders.

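### The planned adjusted analysis picks its covariates by baseline significance tests, a rule that can pass over an imbalance as large as the target effect; prespecified adjustment for the Time 1 score should replace it

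*Protocol article*

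**What the plan says.** All references are to the protocol article.

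- **Baseline tests.** Results plans chi-square and two-tailed t tests of pre-intervention differences between arms. They "will be performed at the student-level and class-level on sociodemographic variables as well as on primary and secondary outcome measures". The significance threshold given in the same section is P < .05.
- **Use of those tests.** The first secondary analysis in Results is "repeating the primary analysis adjusting for any variables exhibiting significant imbalance at baseline to assess whether this influences the findings".
- **Primary model.** Effectiveness is assessed with complex samples procedures and "multi-level (or hierarchical) modeling that includes both fixed (intervention effects) and random (students in classrooms) effects". No baseline covariate is named.
- **Role of Time 1.** Study Design states: "This represents a 3 (time) by 2 (group) repeated measures design". Results lists Time 1 among the three points at which the arms are compared, and Principal Findings says "The primary outcomes are change in anxiety and depression symptoms". Time 1 therefore enters the main comparison as one of the repeated outcomes.
- **Setting.** Five classes were randomized without matching, blocking or stratification, and allocation was stated on the consent forms before Time 1 (Sequence Generation and Allocation Concealment). Time 1 and Time 2 data had been collected when the article was submitted (Results).

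**The concern.** A baseline P value does not measure what matters for adjustment. What matters is how strongly a variable predicts the outcome and how far apart the arms are on it. A strong predictor with a moderate imbalance can escape the test, while a weak predictor can be flagged by chance. In a trial of five unstratified classes, imbalance on prognostic variables is to be expected, so the rule is least dependable where adjustment is most wanted.

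There is also an internal difficulty. The tested variables include the primary outcomes at Time 1. If one is flagged, the rule as written adds that Time 1 score as a covariate to a model in which it is already an outcome.

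At stake are the credibility of the adjusted result, whose content cannot be known in advance, and some precision in a small trial.

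**Working it through.** **Inputs.** From Sample Size: d = 0.30, power .80, alpha .05, expected ICC 0.02 for anxiety and depression-related outcomes, 27 students per class, 90 and 62 students allocated. From Participants: five classes of around 30. The correlation r between Time 1 and follow-up is not given, so .5 to .7 is assumed.

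**1. The plan's own figures.** A two-sample t test at d = 0.30 needs about 175 per arm, not 74 in total. Of the variants tried, the 3 × 2 within-between interaction matches the stated 74: with f = d/2 = 0.15, three measurements and an assumed correlation of 0.5, it gives N = 73, or 74 with equal groups. Then 1 + 26 × 0.02 = 1.52; 74 × 1.52 = 112.5 (stated 112); 112 × 1.10 = 123.2 (stated 123); 123/27 = 4.56. This supports reading the main contrast as group by time with Time 1 included, although the article does not give the mean structure.

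**2. What the tests can detect.** Smallest flagged difference, in SD units:

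- Ordinary student-level t test: 1.976 × √(1/90 + 1/62) = 1.976 × 0.165 = 0.33.
- Student-level test inflated by the plan's design effect: 0.326 × √1.52 = 0.40, before any loss of degrees of freedom.
- Class-level t test, 3 versus 2 classes, 3 df, about 30 per class: 3.182 × √(1/3 + 1/2) × √(0.02 + 0.98/30) = 3.182 × 0.913 × 0.229 = 0.67 (expected threshold).

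An observed difference of 0.30 SD lies below all three.

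**3. What the tests flag by chance.** In 20,000 simulated trials with no true difference (classes of 30, 30, 30 against 31, 31; ICC 0.02), a student-level t test that ignores class rejected in 12% of runs (21% at ICC 0.05). The class-level test held 5%. Even at a true 5% per test, the chance of at least one false flag is 1 − 0.95^k: 51%, 64% and 72% for k = 14, 20 and 25 independent tests (counts and independence assumed).

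**4. Precision.** Student-level residual variance per unit SD²:

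| r (assumed) | change contrast, 2(1 − r) | Time 1 adjusted, 1 − r² | reduction, (1 − r)/2 |
|---|---|---|---|
| .5 | 1.00 | 0.75 | 25% |
| .6 | 0.80 | 0.64 | 20% |
| .7 | 0.60 | 0.51 | 15% |

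The reduction is 35% at r = .3 and 10% at r = .8. It is zero if the repeated-measures model already constrains baseline means to be equal.

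**The case against.** Four points on the other side have force.

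- **The rule is confined to a secondary analysis.** A reader might infer that the primary estimate has its covariates chosen by chance. It does not: the selection feeds only a check on whether adjustment influences the findings. This stands and limits the reach of the point.
- **Baseline is not ignored.** A reader might infer that the Time 1 score is left out of the main analysis. It is there by design, as a level of time. What remains is the difference between a change contrast and baseline adjustment, and only if baseline means are unconstrained.
- **The article is condensed.** Not naming a baseline covariate in the primary model may be settled in a fuller plan, so that silence is not itself a fault. The significance-test rule, however, is stated outright, and further detail elsewhere would not make it sound.
- **The tests may allow for clustering.** Results says generally that the data will be analyzed with clustering taken into account, and class-level tests are planned too. The 12% rate applies only if the student-level tests are ordinary ones. If they do allow for clustering, the detection threshold in step 2 rises, so the rule misses more.

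A reader might also multiply 12% by the number of baseline variables to get a count of false imbalances. The documents do not support that: they give an ICC only for anxiety and depression-related outcomes, not for grades or demographics, and age must cluster by class because the classes come from two school levels.

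**Conclusion.** The point holds for the covariate rule. It selects by significance, can leave a difference as large as the target effect unadjusted (0.30 against a threshold of about 0.33 SD or more), and can place a Time 1 score on both sides of the model. The effect is on the planned adjusted analysis, not on the validity of the primary comparison.

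The precision gain is conditional: student-level residual variance is 15% to 25% lower than for an unconstrained change contrast if r is between .7 and .5. These percentages are not a share of the variance reduction that baseline information could offer. That share, (1 − r)²/r², would run from 18% at r = .7 to 100% at r = .5. They also concern student-level variance only. With five classes, between-class variance and three degrees of freedom limit precision as well.

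Imbalance need not be pure chance either. Families knew the allocation when they consented, so who consented and how Time 1 was answered could differ by arm.

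**What to change.** - Delete the baseline significance tests and the imbalance-driven adjustment. Present baseline data descriptively, by arm and by class.
- In the multilevel model, estimate the arm differences at both Time 2 and Time 3, adjusted for the same scale's Time 1 score, with gender and age as prespecified student-level covariates. Time 1 then leaves the set of outcomes.
- Report the planned unadjusted 3 × 2 analysis as a sensitivity analysis.

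The cost is wording and a small amount of extra analysis; all the variables are already collected. Two downsides should be stated. Time 1 was answered after allocation was known, so the adjusted estimate relies on a baseline that allocation may have influenced. Time 1 and Time 2 data are already in hand, so the change needs a dated, documented reason, made without reference to arm differences in the outcomes.

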## Discussion

### Principal Findings

This paper describes the study protocol of a cluster RCT testing the first adaptation of the UP-A as a school-based anxiety and depression preventive intervention. The primary outcomes are change in anxiety and depression symptoms. Secondary outcomes include change in participant-identified top problems ratings, conduct problems, hyperactivity/inattention symptoms, peer problems, prosocial behavior, school grades, depression and anxiety-related interference, positive and negative affect, anxiety sensitivity, emotional avoidance, life satisfaction, quality of life, self-esteem, school adjustment, and discipline problems. This study will also improve our understanding of factors that might influence the effectiveness of UP-A through the preliminary examination of a number of potential predictors of treatment outcomes, including age, gender, number of sessions attended, engagement and effort during sessions, understanding of basic program concepts, adherence to home practice, and practice of specific strategies outside of sessions.

This study focuses on a school-based, universal prevention program for anxiety and depression, which has the advantage of being easily integrated into a school curriculum and thereby limiting the extent to which participants are segregated from peers and at risk for possible stigmatization due to their participation [74]. It is surprising that, despite the high co-occurrence between anxiety and depression and their shared risk and vulnerability factors, preventive interventions have typically focused on either depression or on anxiety alone [10]. For instance, of the 30 total studies included in a meta-analysis conducted by Ahlen and colleagues, 13 studies focused primarily on depression prevention, 10 studies focused primarily on anxiety prevention, and only 7 studies focused on prevention of both disorders [27]. A transdiagnostic approach to preventing anxiety and depression may enhance the efficacy, generalizability, and cost-effectiveness of prevention programs [10], as well as prevent the development of related emotional disorders.

The location of this research in Spain is particularly significant, as there is a lack of anxiety and depression preventive interventions for youth in the country [70]. A very recent systematic review and meta-analysis on school-based depression and anxiety prevention programs for young people [75] only found 2 studies that took place in Spain, one of them applying a selective preventive intervention and the other applying a universal one. In addition, the current organization of public healthcare in Spain is such that citizens lack direct access to psychological care services due to lengthy waiting lists and a limited number of psychologists [76], although there are some recent initiatives targeting adult populations that aim to implement evidence-based psychological treatments and increase the number of clinical psychologists in primary care [76,77]. Given the high need for mental health services in Spain relative to the number of existing providers, and given the high individual, familial, and societal burden of untreated or undertreated mental health concerns, the development of new and effective preventive intervention programs in the country is crucial.

### Strengths

The greatest strength of this study is that it is the first study to evaluate the effectiveness of the UP-A adapted as a school-based, universal anxiety and depression preventive intervention. In addition, it includes random assignment of clusters (classes) to intervention or WL conditions, implements an evidence-based protocol (the UP-A), uses highly reliable assessment measures, and includes a brief but reasonable window for follow-up after prevention programming (3 months). Another strength of this study is that we are not only examining the effectiveness of the UP-A program in reducing anxiety and depressive symptoms, but we are also examining its impact on a range of other variables. These variables include positive outcomes (quality of life, quality of peer relationships, prosocial behavior, self-esteem, satisfaction with life), which are especially important to measure when working at the universal prevention level, as the majority of participants tend to exhibit non-clinical level concerns [71]. We have also included a measure of personality traits, as the presence of certain personality traits has been identified as a potentially useful means of identifying individuals at risk for developing emotional disorders [78]. Furthermore, this study will not only evaluate the effectiveness of the UP-A program for the total sample of participating students, but it will also conduct preliminary analyses to investigate whether the program is more beneficial for certain groups of adolescents than others (eg, those with higher anxiety and depression at pre-treatment) and will examine predictors of treatment efficacy.

### Limitations

This study has certain limitations due to its preliminary nature. The major limitation of this study is its moderate sample size (152 adolescents across 5 classes were randomized). In addition, the adolescents were recruited from only one school, which may limit generalizability of findings. Furthermore, due to financial and personnel constraints, this study only incorporated adolescent self-report measures. Although this methodology facilitates assessment of a large cohort of adolescents in a relatively short time frame [9], it also has limitations (eg, relies on subjective perceptions), and future studies should consider using information from multiple sources (interviews with the students, parents, and teacher reports, etc). In addition, participants were not blinded to allocation when measures were obtained due to constraints established by the Ethical Research Committee, which specified that informed consent forms must state group allocation. Lastly, using the same group leaders to administer the intervention for all classes increases consistency but, at the same time, may limit generalizability of findings [65].

